### 1.2.7. Expected Side Effects

The main "side effects" expected in relation to DC/Gal or iPS-NKT cells and examples of treatments are listed below.

- ① Elevated blood pressure: Antihypertensive agents should be administered according to symptoms and severity.
- ② Fever: Blood test, chest X-ray, blood culture should be performed. Regarding the possibility of infectious disease, antibiotic agents should immediately be administered. Antipyretics should not be administered if there is no febrile distress but should be given as needed if febrile distress is marked.
- ③ Respiratory distress: Administer oxygen promptly to stabilize blood oxygenation. Blood tests, X-rays and CT scan (contrast if possible) should be performed as part of the screening for the diagnosis. Possible causes of severe respiratory failure during infusion include allergic and embolic events (especially when iPS-NKT is administered). Steroids and epinephrine should be administered according to the severity of the disease, as well as antithrombotic therapy for embolism.
- ④ Shock: The physician in charge and the attending physician will respond promptly. Check vital signs, perform blood tests, and administer steroids or epinephrine according to the severity of the illness. Administer oxygen and pressor agents for respiratory failure and hypotension, depending on the severity of the illness.
- ⑤ Pharyngeal fistula: Since pharyngeal fistula associated with tumor shrinkage was observed in a previous study of combination therapy with autologous NKT cells and DC/Gal, this adverse event should be kept in mind in this study as well. If this adverse event is observed, infection prophylaxis and, if necessary, pharyngeal fistula closure should be performed.
- ⑥ Cerebral infarction: Because the cells are administered into the arteries of the neck, there is a possibility of blood clots flowing into the brain during cannulation. The patient should be evaluated after consulting a neurosurgeon for functional impairment, checking vital signs, and administering cerebro-protective drugs.
- ⑦ Bleeding and hematoma at the puncture site: This may occur with arterial puncture of the cannula. If severe hematochezia develops, consult a plastic surgeon and consider removal of hematochezia. Mild to moderate hematomas can be absorbed with observation.

## 1.3. Rationale

### 1.3.1. Dosing

The results of intravenous administration of  $1 \times 10^6$  and  $2 \times 10^6$  cells/body (20 g) of human iPS-NKT cells to NKT-deficient B6 mice three times on Days 0, 14, and 28, and intravenous administration of mouse DC/Gal  $1 \times 10^9$  cells/m^2 on the same days, showed no death or other safety concerns in either group. The No Observable Adverse Effect Level (NOAEL) of human iPS-NKT cells in combination with mouse DC/Gal was  $2 \times 10^6$  cells/body =  $1 \times 10^8$  cells/kg. This dose is equivalent to  $1 \times 10^8$  cells/kg  $\times 3 \div 3 \times 10^8$  cells/m^2 according to FDA "Guidance for Industry Estimating the Maximum Safe Starting Dose in Initial Clinical Trials." Then assuming a safety margin as 1/10, we set  $3 \times 10^7$  cells/m^2 as the starting dose in this study. In addition, a Phase I study aimed at confirming the

tolerability of iPS-NKT cells alone is ongoing at the time of planning this study (April 2022), and the tolerability of  $3 \times 10^7$  cells/m^2 of iPS-NKT cells has been confirmed. Regarding this result from the Phase I study,  $3 \times 10^7$  cells/m^2 of iPS-NKT cells is appropriate as the starting dose of iPS-NKT cells in this study. The dose of auto-DC/Gal was set at  $1 \times 10^8$  cells, a dose that has been confirmed to be tolerable and safe in combination with autologous NKT cells in previous studies.

Regarding the dosage, the number of administrations of iPS-NKT cell in this study was set to be at once, since the protocol that showed efficacy in previous combination studies of auto-DC/Gal and autologous NKT cells involved one or two doses of auto-DC/Gal followed by one dose of autologous NKT cells. In addition, compared to the intravenous administration in the non-clinical study, the tumor-feeding artery administration is expected to be more effective because of its higher local tumor concentration.

### 1.3.2. Target population

Since this study is an FIH study, patients with recurrent or advanced head and neck cancer who were refractory or intolerant to standard treatment are included in the study based on the "Guidelines for Clinical Evaluation Methods of Antineoplastic Agents" (Pharmaceutical and Food Safety Bureau of Japan, March 31, 2021, #033101). In addition, since the route of iPS-NKT cell administration is defined as tumor-feeding arterial administration, patients with lesions amenable to intravenous infusion and evaluable are set as the selection criteria.

### 1.3.3. Endpoint

Since this is an FIH study, we decided to evaluate the tolerability of the combination of iPS-NKT cell and auto-DC/Gal using a 3+3 design with two doses, the first and second doses. If the number of DLT cases was 1, the same dose was administered to 3 additional cases, and if the number of DLT cases was 2 or more out of 6, the study was terminated. Finally, the MTD will be defined as the maximum dose at which one or fewer DLTs occur in a total of six subjects. In addition, the auto-DC/Gal and iPS-NKT should not be administered to more than 2 subjects on the same day, and auto-DC/Gal and iPS-NKT cell administration in the next subject should be started after an interval of at least 7 days. The above procedure will be used to evaluate DLT, and the Independent Data Monitoring Committee will decide whether to continue the study and the MTD after evaluating all adverse events and other safety information including DLT.

In a preclinical pharmacokinetic study using iPS-NKT cell, the concentration of iPS-NKT cell in mouse blood decreased to 0.33% of the dose at 48 hours after a single intravenous administration and was not detected thereafter. Therefore, two weeks after administration of iPS-NKT cell is reasonable to assess the Dose Limiting Toxicity.

### 1.3.4. Safety management of subjects

Weight, vital signs, ECOG PS, tumor evaluation, hematology, blood biochemistry, coagulation, urinalysis,

and radiological imaging will be performed throughout the study period. In addition, the DLT assessment period (from auto-DC/Gal administration to day 14 after iPS-NKT cell administration) and day 1 of the observation period will, in principle, require hospitalization to carefully monitor subject safety. The principal investigator (PI) or sub-investigator (SI) may leave the hospital at his/her own discretion only if the patient does not develop non-hematologic toxicity or hematologic toxicity of Grade 2 or higher and Grade 3 or higher on or after Day 7 of iPS-NKT cell administration, and be able to contact the study site and home doctor of the subjects, if any, in the event of an adverse event.

Based on the above, we have determined that it is ethically and scientifically appropriate to conduct this study.

## 2. Objective and necessity of Study

Although the combination therapy of iPS-NKT cell and auto-DC/Gal has been confirmed to inhibit tumor growth in preclinical studies and to be safe to a certain degree in mice, there has been no experience with human administration to date. Therefore, it is necessary to explore the tolerability, safety, and efficacy of the combination therapy of iPS-NKT cell and auto-DC/Gal in human for future development, as well as the immunological kinetics induced by experimental therapy. This study will be conducted primarily to confirm the tolerability of the combination therapy by assessing the DLT at the administered dose, and secondarily to confirm the safety profile and efficacy evaluation, as well as to explore the immunokinetic of the combination therapy.

## 3. Study Subjects

Patients who meet all of the following selection criteria and none of the exclusion criteria will be considered eligible subjects.

### 3.1. Inclusion Criteria

Patients who meet all the following criteria will be eligible.

- 1) Patients with recurrent or advanced head and neck cancer, refractory or intolerant to standard of care and who have evaluable lesions that can be treated with intra-arterial infusion to tumor.
- 2) Patients who have not been on previous therapy within 1 month. Any type of previous treatment is acceptable.
- 3) Patients must be at least 20 years old but less than 80 years
- 4) Patients must have an ECOG Performance Status of 2 or less.
- 5) Patients who meet the following laboratory data. Hemoglobin  $\geq 10$  g/dL, White blood cell count  $\geq 3000/\mu\text{L}$  and platelet count  $\geq 75,000/\mu\text{L}$ , Serum creatine  $\leq 1.5$  mg/dL, Total bilirubin  $\leq 1.5$  mg/dL, AST (GOT), ALT (GPT)  $< 2.5$  times the upper limit of facility reference values, SpO2 (under room air)  $\geq 93\%$ .

- 6) Patients who are expected to have a prognosis of 3 months or more.
- 7) Patients for whom written consent has been obtained from the individual.

#### 【Rationale】

- 1) Patients with recurrent or advanced head and neck cancer who were refractory or intolerant to standard treatment are included in the study based on the "Guidelines for Clinical Evaluation Methods of Antineoplastic Agents" (Pharmaceutical and Food Safety Bureau of Japan, March 31, 2021, #033101). In addition, since the route of iPS-NKT cell administration is defined as tumor-feeding arterial administration, patients with lesions amenable to intravenous infusion and evaluable are set as the selection criteria.
- 2-5) Considering the safety and ethics of the subject, and data reliability
- 6) Considering the duration of the study, it was set as the minimum period considered necessary to evaluate the tolerability and safety of the study treatment.

### 3.2. Exclusion Criteria

Patients who meet any of the following conditions are not eligible.

- 1) Patients who are HBs, HCV, HIV or HTLV-1 antibody-positive or HBs antibody-negative but have HBV-DNA detected by HBV-DNA quantitative testing.
- 2) Patients who have been taking or injecting corticosteroids (methylprednisolone 10 mg/day or higher or equivalent) or immunosuppressive drugs within at least 2 weeks prior to the start of the study product.
- 3) Women who are pregnant, lactating, or planning to become pregnant during the study and men who do not agree with using any of effective contraceptive methods under the guidance of a physician during the study period or up to 14 days after the last dose of the study product.
- 4) Patients with active autoimmune disease requiring systemic or immunosuppressive therapy with corticosteroids or biologic agents.
- 5) Patients who have experienced immune-related adverse events with immune checkpoint inhibitors.
- 6) Patients with poorly controlled diabetes mellitus.
- 7) Patients with severe lung disease (mMRC Breathlessness Scale Grade 2 or higher) or with a history of non-infectious interstitial lung disease requiring steroid treatment.
- 8) Patients with significant cardiac disease (NYHA class III or greater).
- 9) Patients with concurrent multiple cancers.
- 10) Patients who are unable to use contrast agents in radiograph (e.g., allergy, kidney disfunction).
- 11) Patients with a history of hypersensitivity to human serum albumin products or proteins of foreign origin.
- 12) Patients who, at the time of informed consent, are participating in other clinical trials or clinical studies and are receiving other investigational products or are judged by the PI or SI to have residual effects of adverse events

 If HCV antibody is positive, HCV-RNA quantification test is performed and negative result is acceptable for inclusion.

 Women of childbearing potential include all women who have experienced menarche, have not undergone sterilization procedures (hysterectomy, bilateral tubal ligation or bilateral oophorectomy, etc.), and have not reached menopause. Menopause is defined as no menstruation for at least 12 consecutive months without any other medical reason.

caused by such products.

- 13) Patients with completely identical genotypes of HLA-A, B and C to the investigational product.
- 14) Patients who are prohibited with blood apheresis because of comorbidities such as unstable angina, A-V block class 2 or greater, WPW syndrome, complete left bundle branch block, systolic blood pressure of 90 mmHg or less, or 170 mmHg or more.
- 15) Patients who are judged to be unsuitable to participate in the study.

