| Exclusion criterion | 
Patients who meet any of the following conditions are not eligible.
 
 
1) Patients who are HBs, HCV, HIV or HTLV-1 antibody-positive or HBs antibody-negative but have HBV-DNA detected by HBV-DNA quantitative testing.
 
2) Patients who have been taking or injecting corticosteroids (methylprednisolone 10 mg/day or higher or equivalent) or immunosuppressive drugs within at least 2 weeks prior to the start of the study product.
 
3) Women who are pregnant, lactating, or planning to become pregnant during the study and men who do not agree with using any of effective contraceptive methods under the guidance of a physician during the study period or up to 14 days after the last dose of the study product.
 
4) Patients with active autoimmune disease requiring systemic or immunosuppressive therapy with corticosteroids or biologic agents.
 
5) Patients who have experienced immune-related adverse events with immune checkpoint inhibitors.
 
6) Patients with poorly controlled diabetes mellitus.
 
7) Patients with severe lung disease (mMRC Breathlessness Scale Grade 2 or higher) or with a history of non-infectious interstitial lung disease requiring steroid treatment.
 
8) Patients with significant cardiac disease (NYHA class III or greater).
 
9) Patients with concurrent multiple cancers.
 
10) Patients who are unable to use contrast agents in radiograph (e.g., allergy, kidney dysfunction).
 
11) Patients with a history of hypersensitivity to human serum albumin products or proteins of foreign origin.
 
12) Patients who, at the time of consent acquisition, are participating in other clinical trials or clinical studies and are receiving other investigational products or are judged by the PI or SI to have residual effects of adverse events caused by such products.
 
13) Patients with completely identical genotypes of HLA-A, B and C to the investigational product.
 
14) Patients who are prohibited with blood apheresis because of comorbidities such as unstable angina, A-V block class 2 or greater, WPW syndrome, complete left bundle branch block, systolic blood pressure of 90 mmHg or less, or 170 mmHg or more.
 
15) Patients who are judged to be unsuitable to participate in the study.
 
 |

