#### 【Rationale】

- 1) When iPS-NKT cells are administered intravenously, they have been found to accumulate in the liver. In this study, iPS-NKT cells were administered intravenously into tumor-feeding arteries, and although it is expected that there will be little systemic circulation, the eventual effect on the liver cannot be ruled out, and therefore, this setting was determined based on consideration of the safety of the subjects.
- 2, 4-5) The iPS-NKT cells are intended for direct and indirect immune activation in the target patients and were set up to exclude the influence of diseases and drugs that affect the immune status of the target patients.
- 3) Since the effects of iPS-NKT cells on the fetus and fertility have not been confirmed to date, the dose was set to avoid such effects in the target population. Since iPS-NKT cells administered into the body are considered to be almost completely eliminated from the body on the seventh day after administration, a contraceptive period was established.
- 6-8) Considering the safety of the subjects.
- 9) This was established to exclude the impact of adverse events due to cancers other than head and neck. The time period was set based on the recurrence rate after curative treatment of gastrointestinal cancer, which is a particularly frequent overlapping cancer of the head and neck, and because the risk of recurrence is considered to be high within 2 years.
- 10) Since the use of contrast enhancements is mandatory in this study to confirm tumor-feeding arteries in the subject
- 11) Considering the subjects' safety
- 12) To exclude the effects by other experimental agent on other clinical trials.
- 13) Considering the PK/PD analysis, we need to detect the iPS-NKT cells with different genotype from subjects one.
- 14) Because it is impossible to conduct this study in patients who are unable to have component blood samples taken for DC/Gal preparation.
- 15) Other settings were made to allow for exclusions when the investigators judged that the study could not be safely conducted.

---

 The genotype of iPS-NKT cell used in this study is as follows:  
A\*26:01-B\*35:01-C\*03:03  
A\*26:03-B\*35:01-C\*03:03

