| DLTs under hospitalization g)  |   |            |              | ←————→           |    |   |   |    |    |                                  |                 |    |             |
| HLA test                                  |   | ●          |              |                  |    |   |   |    |    |                                  |                 |    |             |
| Anti-HLA antibody                         |   | ●          |              |                  | ●  |   |   |    |    | ●                                |                 |    | ●           |

(a) Perform only in women of childbearing potential. Perform a urine qualitative test.

(b) Infectious disease tests include HIV antibody, HTLV-1 antibody, HBs antigen, HBs antibody, HBc antibody, and HCV antibody. If the HBs antigen is negative and the HBs antibody test or HBc antibody test is positive, the HBV-DNA quantitative test is performed. If the HCV antibody test is positive, the HCV-RNA quantitative test is performed.

(c) Secure the route of administration of the investigational product 1 week prior to the first administration date (allowance based on 1 week prior to the first administration date: -14 to +7 days). As described in the Administration Method section, there are two methods of administering the investigational product (method of securing the route of administration): the port method (e.g., for maxillary cancer) or the Selsinger method. In the case of the port method, a port is implanted under local anesthesia in an IVR room, and the investigational product is administered through the implanted port after confirming that there are no signs of infection in the wound. In the case of the Selsinger method (tongue cancer, etc.), the tip of the catheter is guided into the tumor-feeding artery in the IVR room, and the investigational product is administered directly.

(d) Vital signs shall include body temperature, pulse rate, respiratory rate, SpO2, and blood pressure (systolic and diastolic), and additional tests (chest X-ray, hematological and serological tests, blood gas tests, etc.) may be added as necessary based on the judgment of the PI or SI.

(e) The blood collection schedule for PK/PD and blood cytokine measurements will be as shown in Table 20

(f) Isolate PBMCs from blood samples and stain for cell surface markers.

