### 7.1.1. Screening test

After obtaining consent, the screening tests are initiated. The PI or SI will perform the following screening tests and enroll patients who meet the selection criteria and do not violate the exclusion criteria. The test items shall be as described below.

- Body weight (usu. one's own)
- Vital signs
- ECOG PS
- Hematological examination
- Blood biochemical tests (including HbA1c)
- Coagulation test
- Urinalysis
- Pregnancy test (for women of childbearing potential only)
- Infectious disease test (HBs antigen, HBs antibody, HBc antibody, HCV antibody, HIV antibody or HTLV-1 antibody)
- 12-lead ECG test
- Chest X-ray
- Contrast-enhanced CT scan (vascular and tumor evaluation)
- HLA testing (up to area 2 by Luminex method)
- Anti-HLA antibody test

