| infectious disease test
(*only at screening)                               | HBs antigen, HBs antibody, HBc antibody, HCV antibody, HIV antibody or HTLV-1 antibody, or
HBV-DNA quantification (*Added when HBs antigen negative and HBs or HBc antibody positive)
HCV-RNA quantification (*Additional when HCV antibody positive)                                                                                                                                                                                                                                                                                                                                                                                                                                                                                                                          |
| HLA test
(*only at screening)                                              | HLA genes (HLA-A, B, C, DRB1, DQB1, DPB1)                                                                                                                                                                                                                                                                                                                                                                                                                                                                                                                                                                                                                                                                                                                                            |

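### Exclusion criterion 1 turns on HBs antibody but the HBV-DNA testing rule turns on HBs antigen, so an antigen-positive, antibody-negative patient is neither automatically excluded nor sent for HBV-DNA

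*Protocol*

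**What the plan says.** **The eligibility rule.** The synopsis gives exclusion criterion 1 as "Patients who are HBs, HCV, HIV or HTLV-1 antibody-positive or HBs antibody-negative but have HBV-DNA detected by HBV-DNA quantitative testing". Section 3.2 uses the same hepatitis B wording, "HIV or HTLV-1 antibody-positive or HBs antibody-negative but have HBV-DNA detected by HBV-DNA quantitative testing", and adds a footnote for HCV only: "If HCV antibody is positive, HCV-RNA quantification test is performed and negative result is acceptable for inclusion". HBs antigen appears in none of the fifteen exclusion criteria.

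**The tests.** Section 7.1.1 lists the screening infection panel as "HBs antigen, HBs antibody, HBc antibody, HCV antibody, HIV antibody or HTLV-1 antibody", so the antigen is measured in every screened patient. Footnote (b) of the study calendar (section 7.1) sets the reflex test: "If the HBs antigen is negative and the HBs antibody test or HBc antibody test is positive, the HBV-DNA quantitative test is performed". The laboratory test list in section 7.1.3 has the same trigger: "Added when HBs antigen negative and HBs or HBc antibody positive".

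**The purpose.** The rationale in section 3.2 for criterion 1 is that infused cells may reach the liver and that "the eventual effect on the liver cannot be ruled out".

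**The concern.** The rule that decides entry and the rule that orders the test branch on different markers. A positive result on a measured hepatitis B marker can therefore have no stated eligibility consequence, and a test can be ordered whose result changes nothing. The criterion exists for liver safety, so the first of these matters more.

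Eligibility wording also has later effects. Under section 5.9.2, a subject found ineligible after registration is taken off study. Under section 10.1.3, a violation of an exclusion criterion removes the subject from the per protocol set. Section 10.2 caps the analysed patients at 12, so a criterion that can be read two ways may affect who is treated and who is counted.

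**Working it through.** There is no planned figure to reproduce. The check runs each marker pattern through the two rules as written.

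**Inputs**
- Criterion 1 (synopsis; section 3.2): exclude if HBs antibody is positive; if it is negative, exclude only when HBV-DNA is detected.
- HBV-DNA trigger (calendar footnote (b); laboratory test list, section 7.1.3): mandated if HBs antigen is negative and either HBs or HBc antibody is positive.
- Comparator: criterion 1 with antigen in place of antibody and the same trigger. It serves only to measure the mismatch and is not a proposed rule.

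**Enumeration.** Three markers with two results each give 2 × 2 × 2 = 8 patterns.

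| HBs antigen | HBs antibody | HBc antibody | HBV-DNA mandated | Criterion 1 as written | Antigen-keyed comparator | Same? |
|---|---|---|---|---|---|---|
| + | + | + | no | excluded | excluded | yes |
| + | + | − | no | excluded | excluded | yes |
| + | − | + | no | not automatically excluded | excluded | no |
| + | − | − | no | not automatically excluded | excluded | no |
| − | + | + | yes | excluded | excluded only if DNA detected | no |
| − | + | − | yes | excluded | excluded only if DNA detected | no |
| − | − | + | yes | excluded only if DNA detected | excluded only if DNA detected | yes |
| − | − | − | no | not excluded | not excluded | yes |

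**Reading the table**
- Antigen-positive, HBs antibody-negative: 2 of 8 patterns. The antibody limb does not apply. The HBV-DNA limb needs a result that the plan does not require anyone to obtain.
- Antigen-positive, HBs antibody-positive: 2 of 8 patterns. Excluded, but because of the antibody.
- HBV-DNA is mandated in 3 of 8 patterns. In 2 of those 3 the patient is already excluded by the antibody, so the result cannot alter eligibility. In the third (antigen-negative, HBs antibody-negative, HBc antibody-positive) it decides eligibility.
- The two versions of the rule disagree in 2 + 2 = 4 of 8 patterns.

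The patterns are not equally common, so 4 of 8 counts rule outcomes and is not a share of patients.

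**The case against.** **An antigen-positive patient would be noticed.** The antigen result is available before registration. Section 5.4.2 requires the investigator to consult at least two coordinating-committee physicians on eligibility. Criterion 15 lets anyone judged unsuitable be excluded, and section 7.1.3 allows extra tests, serological ones included. The testing plan does not forbid HBV-DNA outside its trigger, and a detected result in any HBs antibody-negative patient would exclude through criterion 1. Inclusion criterion 5 also limits AST, ALT and bilirubin. All of this stands and makes unnoticed entry unlikely. But these are discretionary or indirect protections, and none of them says what a positive HBs antigen means for eligibility.

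**It is a translation slip.** That is plausible: the English text still contains Japanese fragments. It is not established, and the antibody wording is the current text in both the synopsis and section 3.2.

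**Three stronger readings are not supported.**
- A reader might infer that all antigen-positive patients escape criterion 1. Those who are also HBs antibody-positive are excluded through the antibody; the gap is confined to the antibody-negative ones.
- A reader might infer that antibody-positive patients with undetected HBV-DNA were meant to be eligible. The HCV footnote gives such a route explicitly; nothing comparable is written for hepatitis B. Excluding all antibody-positive patients costs recruitment, not safety. What stands is only that the ordered test has no eligibility role for them.
- A reader might infer a distortion of the primary endpoint, since one hepatic event in a cohort of six could move 1/6 to 2/6. That is true of any single DLT and is not specific to this wording. It would also require such a patient to be enrolled, to have an event meeting section 5.2 within the DLT period, and to have it attributed to the product despite the monitoring committee's final judgement under section 10.6. The protocol gives no probability for any of these steps.

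**Conclusion.** The inconsistency is real and sits in an operative safety criterion. For HBs antigen-positive, HBs antibody-negative patients (2 of 8 patterns), following the protocol to the letter gives no mandatory HBV-DNA test and no automatic exclusion. For antigen-negative, HBs antibody-positive patients (2 of 8), it orders a test that cannot affect entry.

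This rests on the grammatical reading of criterion 1, in which antibody-positive governs all four viruses named. Reading the first mention of HBs as antigen would not settle the matter. The second limb still says "HBs antibody-negative but have HBV-DNA detected by HBV-DNA quantitative testing", so an antigen-negative, antibody-positive patient with detected HBV-DNA would then meet neither limb.

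The number of patients affected cannot be estimated from the protocol. The point concerns eligibility and safety screening; the 3+3 sample size of 2 to 12 is unaffected.

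**What to change.** - Check the source-language text of criterion 1 to see whether antibody or antigen was meant in each place.
- Reconcile criterion 1 in the synopsis and section 3.2 with calendar footnote (b) and the laboratory test list in section 7.1.3. Each combination of HBs antigen, HBs antibody, HBc antibody and HBV-DNA should lead to one stated eligibility outcome; a short table would do.
- Require HBV-DNA wherever the stated outcome depends on it, and state what the result means for entry wherever the test is ordered.
- Re-check subjects already enrolled against the reconciled text and record any discrepancy.

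The choice of hepatitis B rule belongs to the investigators; this review does not propose one. The cost is mainly an amendment to wording, because the markers and the HBV-DNA test are already in the screening plan, plus a review of existing screening records for a study of at most 12 analysed patients.
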